HCQ [12]. The potential antiviral and anti-inflammatory properties of HCQ, along with the low cost, very good oral bioavailability, higher concentrations in the lungs relative to the plasma levels and acceptable safety profile supported the formulation this national advisory. After getting informed consent the drugs will be dispensed directly to the participants during the COVID-19 screening clinic visit or through door step delivery by the concerned HCW with help of the police officials. They will be followed up for 4 weeks telephonically or physically when require and will be enquire regarding development of any COVID-19 symptoms like fever, cough, sore throat, shortness of breath, diarrhea, myalgia or any adverse drug event. During follow up nasopharyngeal and or throat swab of the participants will be taken for processing reverse transcription polymerase chain reaction (RTPCR) for the detection of SARS-Cov-2 RNA to confirm the diagnosis of CoVID-19. Samples for RTPCR will be taken when any asymptomatic participants become symptomatic and by the 5-14 days of contact in asymptomatic participants through in-hospital visit at COVID-19 screening clinic at EMOPD and the institute's communicable disease ward isolation. Only the participant with RTPCR positive for SARS-CoV-2 and with or without symptoms will be defined as definite COVID-19 case. The participant with new onset symptoms, but RTPCR negative for SARS-CoV-2 or cannot be performed for any reason will be defined as probable COVID-19 case. Both the definite and probable COVID-19 cases together are defined as COVID-19 case. Asymptomatic participants with negative RTPCR will be defined as non-COVID case. Incidence of COVID-19, definite COVID-19 and probable COVID-19 in previously asymptomatic participants will be compared between the PEP and control groups. Baseline routine investigations (blood, CXR, ECG) at upfront may not be possible as each participant will be the potential source of SARS-CoV-2 and additional contact with HCW will spread the virus to the healthy individual. ECG will be offered to each participant at baseline and at the end of the study. Participants will be interviewed during the follow up for any adverse events and ECG will be repeated as per indication. During follow up if any individuals become symptomatic then all relevant investigations will be done as per indications. The participants, who turned out to be definite COVID-19, were shifted to the Nehru Hospital Extension (NHE), a dedicated COVID-19 centre, of the institute PGIMER, Chandigarh and managed as per institutional COVID-19 protocol. Participant

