
with Probable COVID-19 were advised to continue with home quarantine. The participants with new onset COVID-19 will be managed as per institute's COVID-19 management protocol and the participants needing admission will be given best possible medical care in the institute's SARI/Nehru extension COVID ward under isolation.

**Primary outcome:** Incidence of COVID-19, definite COVID-19 & probable COVID-19

**Secondary outcome:** 1. New onset symptoms of COVID-19, 2. Compliance to the advised therapy, 3. Number of difficulty faced during quarantine, 3. Incidence of adverse drug reaction

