**Sample size & statistical analysis:**

As per recently concluded our institutional pilot study, the incidence of COVID-19 was significantly ( $P = 0.033$ ) lower in the PEP group (10.6%) that received HCQ prophylaxis compared with the control group (19.5%). The total absolute risk reduction for the incidence of COVID-19 in participants received PEP with HCQ was  $-8.9\%$  points [13]. Anticipating at least 20% incidence of COVID-19 in control group as compared to 10% incidence rate in PEP group the total sample size will be around 400 (200 each group), when there will be 80% (power) chance of detecting a significant difference between the two groups at a one-sided 0.05 significance level ( $\alpha$ -error of 5%). Anticipating 10% dropout we will try to recruit total 440 participants for the study. However as per protocol, after following strict inclusion and exclusion criteria the final sample size for the data analysis may reduce further. Final power of the study may be recalculated after getting actual response/outcome at the end of the clinical trial through post-hoc statistical power analysis. Randomization will be done with the help of computer generated random number in a block randomization pattern in a block of 10 patients (5:5). Randomization and treatment concealment will be done by the pharmacologist. The data will be managed in data base system through Microsoft Excel and statistical analysis will be performed by SPSS 21.0 version. The parametric data will be

analyzed by paired or unpaired “t”-test and the binominal/categorical endpoints will be analyzed with non-parametric chi-square test with yet’s correlation and the proportions will be compared by Fisher’s exact test. The relative risk (RR) and number needed to treat (NNT) will be determined for the safety and risk assessment. The p-value less than 0.05 will be considered statistical significant (95% CI).

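### The protocol lists a composite and both its components as the primary outcome, compares each at p < 0.05, and never says which one decides the trial

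*Protocol*

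**What the plan says.** All references are to the Protocol, Part II, section 6 (Details of method).

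- **Primary outcome.** Three incidences stand under one heading, with no order: "Incidence of COVID-19, definite COVID-19 & probable COVID-19".
- **Method and intervention, definitions.** A definite case is RT-PCR positive, with or without symptoms. A probable case has new symptoms with RT-PCR negative or not done. Then: "Both the definite and probable COVID-19 cases together are defined as COVID-19 case".
- **Method and intervention, comparisons.** "Incidence of COVID-19, definite COVID-19 and probable COVID-19 in previously asymptomatic participants will be compared between the PEP and control groups".
- **Sample size & statistical analysis, tests.** Categorical endpoints are to be analysed by "non-parametric chi-square test with yet’s correlation and the proportions will be compared by Fisher’s exact test".
- **Sample size & statistical analysis, threshold.** "The p-value less than 0.05 will be considered statistical significant (95% CI)". This is the only decision threshold given for the analysis.
- **Sample size & statistical analysis, planning.** "Anticipating at least 20% incidence of COVID-19 in control group as compared to 10% incidence rate in PEP group", giving "the total sample size will be around 400 (200 each group)". These are composite rates. No planned rate is given for definite or probable COVID-19.

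**The concern.** The protocol does not say whether the trial succeeds when the composite is significant, when any one of the three is, or only when all are. Followed as written, a significant result on any of the three is a significant result on a primary outcome. That raises the chance of a false finding above that of a single test.

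The three also make a poor set of equals. A participant with symptoms counts as definite or probable according to the RT-PCR result, or to whether the swab could be processed at all. Differences in testing can therefore lower one component and raise the other without any change in illness. A significant difference in probable COVID-19 alone would have no clear meaning for efficacy.

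**Working it through.** **1. The protocol's own figure.** With p1 = 0.20, p2 = 0.10, mean 0.15 and 80% power:

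n per arm = [z_α √(2 × 0.15 × 0.85) + z_β √(0.20 × 0.80 + 0.10 × 0.90)]² / (0.20 − 0.10)²

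- Two-sided 0.05: [1.960 × 0.505 + 0.842 × 0.500]² / 0.01 gives 199 per arm, 398 in total. This matches the stated 400.
- One-sided 0.05: [1.645 × 0.505 + 0.842 × 0.500]² / 0.01 gives 157 per arm, 314 in total. This does not match.

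The text says "one-sided 0.05 significance level", but the number fits a two-sided test, as does the mention of a 95% CI. Error rates are therefore shown both ways. In either case the calculation concerns the composite only.

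**2. Upper reference.** Three independent tests at 0.05 would give 1 − 0.95³ = 14.3%. The outcomes overlap, so the true figure is lower.

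**3. Allowing for the overlap.** Let d and p be the definite and probable rates and c = d + p. The correlations of the test statistics are:

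- definite with probable: −√[dp / ((1 − d)(1 − p))]
- definite with composite: √[d(1 − c) / (c(1 − d))], and likewise for probable

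For d = p = 0.10 these are −0.11 and 0.67. If every test had a true size of 5%, a trivariate normal with these correlations gives an any-of-three rate of 11.7% two-sided and 11.4% one-sided. Across splits from 10/10 to 19/1 the ranges are 10.7% to 11.7% and 10.5% to 11.4%.

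**4. With the actual tests.** I simulated 400,000 null trials per scenario at 200 per arm with 20% composite incidence in both arms. The split is an assumption, because the protocol plans none. The table gives the chance that at least one of the three has p < 0.05.

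| Definite / probable | Chi-square, two-sided | Yates or Fisher, two-sided | Yates or Fisher, one-sided | Composite alone, Yates or Fisher, two-sided |
|---|---|---|---|---|
| 10% / 10% | 11.6% | 8.4% | 8.5% | 3.7% |
| 15% / 5% | 11.4% | 7.8% | 8.0% | 3.7% |
| 5% / 15% | 11.5% | 7.9% | 8.1% | 3.7% |
| 18% / 2% | 10.6% | 6.4% | 6.6% | 3.6% |
| 2% / 18% | 10.8% | 6.5% | 6.7% | 3.7% |

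Yates and Fisher gave the same rates at this sample size. A single uncorrected chi-square test of the composite gives about 5%.

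**5. Direction.** With two-sided tests, the chance of at least one false finding in favour of HCQ is about half: roughly 3% to 4% with Yates, against about 1.8% for the composite alone, and roughly 5.5% to 6% with uncorrected chi-square, against about 2.5%.

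**The case against.** **The composite is the evident primary outcome.** The primary objective speaks only of COVID-19, the composite is listed first, and the pilot rates and power are stated for it. One can read the plan as a single powered composite reported with its components. That is a reasonable guess at the intention, but the text does not say it. It puts all three under the primary heading and plans to compare all three.

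**Ordering or adjustment may be in an SAP.** This stands in part. The lack of an adjustment method in the protocol is not itself a fault. Choosing the primary outcome is a protocol decision, however, and this protocol made it by naming three.

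**A reader might infer that the false-positive rate is 11%.** The documents do not support that as the rate under the plan. It assumes tests of true size 5%, such as uncorrected chi-square, whereas the protocol names Yates and Fisher, which are conservative at these counts. With two-sided tests the figure also counts false findings of harm. Under two-sided Yates tests the chance of a false benefit finding stays below 5%, although it is above that of a single test. The 11% keeps some relevance: the three P values in eTable 1 (0.968, 0.460, 0.187) are reproduced from its counts by uncorrected chi-square, while Yates gives 1.00, 0.567 and 0.316.

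**A reader might also infer from eTable 1 that a conclusion was picked after the fact.** From its counts the relative risks are (16/569)/(21/587) = 0.79 for definite, (7/569)/(3/587) = 2.41 for probable and (23/569)/(24/587) = 0.99 for the composite. The components do point in opposite directions. None of the comparisons is significant, though, and there are only 10 probable events. The table illustrates the ambiguity and shows no false claim.

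**Conclusion.** The point holds as a defect in how the primary outcome is fixed: three overlapping outcomes, one threshold, no stated decision rule, and a sample size that covers only one of them. Under the named tests the any-of-three error rate is about 6% to 8.5%, roughly double that of a single test of the composite and above 5%. The 11% is a nominal figure.

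These sizes rest on 200 per arm, 20% composite incidence and the assumed definite/probable splits. Splits with one very rare component lie at the low end. How much of the error favours HCQ depends on sidedness, on which the protocol is inconsistent.

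**What to change.** In the Primary outcome paragraph, name one decisive outcome. There are two workable routes:

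- **Composite COVID-19 as the sole primary outcome.** The 20% versus 10% assumption and the 400 participants already describe it, so the stated sample size is kept. Move definite and probable COVID-19 to the secondary outcomes, reported with estimates and 95% CIs. If a claim on definite COVID-19 is wanted, test it second in a fixed sequence, only if the composite is significant. Make no standalone claim on probable COVID-19.
- **RT-PCR-confirmed COVID-19 as the sole primary outcome.** The sponsor must then state the expected definite rate in each arm and restate the power. Neither is in the protocol, so the power at 200 per arm is at present unknown.

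The first route is a short edit to the outcome paragraph; the second also reopens the sample size. Splitting alpha is possible but costly. Bonferroni at 0.05/3 for 20% versus 10% needs 266 per arm two-sided (224 one-sided), and at 200 per arm the power falls to 66% (75% one-sided).

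The downside of naming one outcome is that a favourable result on a component alone can no longer support a claim.

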**Secondary objectives:**

1. New onset symptoms of COVID-19
2. Compliance to the therapy
3. Difficulty faced during quarantine
4. Adverse drug reaction monitoring

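### The only listed safety outcome is adverse drug reaction, which implies a causal judgement, so a drug-caused symptom that resembles COVID-19 can be left out of the safety comparison

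*Protocol*

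**What the plan says.** Section 5 (Objectives) gives the safety objective as "Adverse drug reaction monitoring". The secondary outcomes in section 6 give the matching endpoint as "Incidence of adverse drug reaction". No outcome covering adverse events of any cause is listed.

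Collection is wider. Section 6, Method and intervention, states: "Participants will be interviewed during the follow up for any adverse events and ECG will be repeated as per indication". The same paragraph says that during follow-up staff will "enquire regarding development of any COVID-19 symptoms like fever, cough, sore throat, shortness of breath, diarrhea, myalgia or any adverse drug event".

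The case definition comes next: "The participant with new onset symptoms, but RTPCR negative for SARS-CoV-2 or cannot be performed for any reason will be defined as probable COVID-19 case". These participants count in the combined outcome: "Both the definite and probable COVID-19 cases together are defined as COVID-19 case".

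The first secondary outcome is new symptoms of COVID-19, so the listed symptoms are compared by arm there. The statistical paragraph of section 6 plans a relative risk and a number needed to treat for safety.

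**The concern.** In a placebo-controlled trial the safety comparison needs no one to decide what caused an event. If every event is counted in both arms, an excess under HCQ appears as a difference between randomised groups. An outcome limited to adverse drug reactions puts an individual causal judgement in front of that comparison.

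The judgement is hard here. Participants are recent contacts of confirmed cases, so a new symptom soon after the first tablets may be early infection or a drug effect. The protocol gives such a symptom a ready label as COVID-19 and does not say whether it also counts as an adverse event. If it does not, the relative risk and number needed to treat for safety are computed without it. Drug-caused symptoms arise only under HCQ, so any such loss falls on that arm and moves the safety comparison towards no difference.

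**Working it through.** The plan states no safety figure to reproduce. The check sets the provisions side by side, then asks what the results tables supplied with the protocol can add.

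**Step 1. What is collected and what is compared.** The interview covers adverse events generally: "Participants will be interviewed during the follow up for any adverse events". The endpoint is "Incidence of adverse drug reaction". The second is narrower if the term has its usual meaning. The protocol does not define it, and also uses adverse drug event and adverse event without definition.

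**Step 2. Where a new symptom goes.** Take a participant who develops diarrhoea after the first-day tablets.
- RTPCR positive: definite COVID-19, with or without symptoms.
- RTPCR negative or not done: probable COVID-19.
- In both cases the participant is a COVID-19 case for the primary outcome, and the symptom falls under the first secondary outcome.
- No step asks whether the drug caused the symptom, and no rule says that it also enters the adverse reaction count.

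The route is not confined to the six named symptoms. The follow-up list gives examples only, and the probable-case rule refers to new symptoms without listing them. eTable 2 also includes headache, joint pain, sneezing and body ache, none of which the follow-up list names.

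**Step 3. Whether the text forces the loss.** It does not. Nothing makes COVID-19 symptom and adverse drug event mutually exclusive, and nothing forbids counting one symptom in both places. The loss is permitted, not prescribed.

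**Step 4. What the results tables show.**

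eTable 2, reports summed over its nine rows:
- Control (N=594): 13 + 8 + 8 + 2 + 2 + 0 + 1 + 1 + 0 = 35
- HCQ (N=574): 10 + 7 + 7 + 3 + 1 + 1 + 0 + 0 + 1 = 30
- Total: 35 + 30 = 65

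Myalgia plus diarrhoea:
- Control: 2 + 0 = 2 reports, 2/594 = 0.34%
- HCQ: 3 + 1 = 4 reports, 4/574 = 0.70%
- Difference: 0.70 − 0.34 = 0.36 percentage points

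These are reports, and one participant may contribute several.

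eTable 1, probable cases among participants in whom RTPCR could be performed:
- Control: 3/587 = 0.5%
- HCQ: 7/569 = 1.2% (stated P = 0.187)

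Under the protocol's definition these ten participants had symptoms and a negative RTPCR. So the category in which a drug-caused symptom could be placed was used. The tables do not give the cause of any symptom. No adverse reaction table is at hand, so it cannot be checked whether these symptoms were also counted there.

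**The case against.** The strongest reply has four parts.

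1. **The wording may simply be loose.** Three terms are used without definition, participants are interviewed about any adverse event, and the Project summary assigns adverse event monitoring to the pharmacology department. The outcome may have been meant to include everything. This stands as a limit: the narrow reading rests on the outcome's name. It also supports settling the wording.

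2. **The follow-up sentence says what to ask, not how to sort answers.** This is correct. A reader might infer that a participant with diarrhoea is necessarily filed under COVID-19 and lost to safety. The documents do not say so.

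3. **The listed symptoms are already compared by arm**, without attribution, under the first secondary outcome. This also stands. An HCQ excess in diarrhoea or myalgia would be visible there, so the protection of the placebo arm is not wholly given up. But the comparison is presented as efficacy, and the safety relative risk would still omit those events.

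4. **Double recording and an all-cause table are usual content for an analysis plan or case report form**, which may exist. That is fair for the mechanics. The endpoint itself, however, is fixed in the protocol, and the point concerns that endpoint.

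RTPCR at symptom onset gives some separation of causes, so it would be too strong to say that attribution is impossible. But a positive test does not exclude a drug effect, and a negative one still leads to a COVID-19 label.

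**Conclusion.** The point holds as a weakness in how the safety outcome is defined. The plan collects adverse events of any kind, names only adverse drug reaction as the endpoint, and labels COVID-19-like symptoms without a drug-cause step. A drug-caused symptom can then count for efficacy alone.

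Two stronger conclusions are tempting. One is that the safety result is biased towards no harm. The other is that eTable 2, or the 7 against 3 probable cases, shows drug effects filed as COVID-19. Neither is supported. The totals of 35 and 30 show no overall excess of reports under HCQ, the myalgia and diarrhoea counts are very small, and no table shows what was left out of the adverse reaction count.

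The size cannot be stated, because the protocol text gives no rate of drug-caused symptoms and no list of expected reactions. The conclusion assumes that adverse drug reaction has its ordinary, attribution-based meaning and that a symptom labelled COVID-19 is not routinely counted as an adverse event as well. If either assumption fails, the gap is one of wording only.

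**What to change.** In the secondary outcomes of section 6, replace the safety outcome with: *incidence of any adverse event from first dose to end of follow-up, by randomised arm, whatever the judged cause*. Keep adverse drug reaction as a reported subset, and bring the safety objective in section 5 into line. Add one sentence saying that each new symptom is counted in the safety total as well as in the symptom outcome. Leave the definitions of definite and probable COVID-19 unchanged.

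The cost is a change of wording and one further table from interviews already planned. The drawback is that adverse event totals in both arms will include COVID-19 illness. Showing the adverse drug reaction subset beside the total, and the symptom outcome as already planned, lets a reader see this.

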**Sample size & statistical analysis:**

As per recently concluded our institutional pilot study, the incidence of COVID-19 was significantly ( $P = 0.033$ ) lower in the PEP group (10.6%) that received HCQ prophylaxis compared with the control group (19.5%). The total absolute risk reduction for the incidence of COVID-19 in participants received PEP with HCQ was  $-8.9\%$  points [13]. Anticipating at least 20% incidence of COVID-19 in control group as compared to 10% incidence rate in PEP group the total sample size will be around 400 (200 each group), when there will be 80% (power) chance of detecting a significant difference between the two groups at a one-sided 0.05 significance level ( $\alpha$ -error of 5%). Anticipating 10% dropout we will try to recruit total 440 participants for the study. However as per protocol, after following strict inclusion and exclusion criteria the final sample size for the data analysis may reduce further. Final power of the study may be recalculated after getting actual response/outcome at the end of the clinical trial through post-hoc statistical power analysis. Randomization will be done with the help of computer generated random number in a block randomization pattern in a block of 10 patients (5:5). Randomization and treatment concealment will be done by the pharmacologist. The data will be managed in data base system through Microsoft Excel and statistical analysis will be performed by SPSS 21.0 version. The parametric data will be

analyzed by paired or unpaired “t”-test and the binominal/categorical endpoints will be analyzed with non-parametric chi-square test with yet’s correlation and the proportions will be compared by Fisher’s exact test. The relative risk (RR) and number needed to treat (NNT) will be determined for the safety and risk assessment. The p-value less than 0.05 will be considered statistical significant (95% CI).

**Ethical justification:** Being a tertiary care centre we are catering many states which include Punjab, haryana, himachal Pradesh, Uttarakhand, Uttar Pradesh. This put our institute to handle highest burden of suspected cases of SARS-CoV-2 in northern India. At present there is no definitive therapeutic drugs or vaccine are available for the treatment of SARS-CoV-2. Among all the used drugs HCQ has given some rays of hope to battle against this deadly pandemic. Prolong use of HCQ has been found to be quite safe and we are giving HCQ for 3 weeks only and that too weekly with total cumulative dose of 2000 mg only. Our own institutional study showed that HCQ has the potential for the prevention of COVID-19 in house direct contacts of laboratory confirmed COVID-19 cases [13]. All the patients will receive standard best possible medical therapy. The study is not intended to do any invasive procedure or increase the cost of therapy. Study is intended to prevent emergence of SARS-CoV-2 infection in asymptomatic patients with chemo-prophylaxis. Only those individual with high risk for developing infection will be included after getting informed consent. As a research institute of national as well as international interest, it is a great opportunity for us to produce such a robust data which can be utilized in reforming national and international guidelines for the battle against of SARS-CoV-2 pandemic.

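### The sample size of 200 per group does not follow from the stated one-sided 0.05 level, and the protocol's significance rule implies a two-sided test

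*Protocol*

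**What the plan says.** Everything is in one paragraph of the protocol, under Sample size & statistical analysis (section 6).

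- Design rates: "Anticipating at least 20% incidence of COVID-19 in control group as compared to 10% incidence rate in PEP group".
- Size: "the total sample size will be around 400 (200 each group"), with equal allocation ("in a block of 10 patients (5:5")).
- Power and level: "when there will be 80% (power) chance of detecting a significant difference between the two groups at a one-sided 0.05 significance level".
- Decision rule, at the end of the paragraph: "The p-value less than 0.05 will be considered statistical significant (95% CI").

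For categorical endpoints the paragraph names a chi-square test with what is evidently Yates' correction, and Fisher's exact test for proportions. It does not say which of them decides the primary comparison, or whether the tests are one- or two-sided. It also reports the pilot rates of 19.5% (control) and 10.6% (HCQ) as background to the design rates.

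**The concern.** All the inputs to the calculation are printed, so the result can be checked, and 200 per group is well above what a one-sided 0.05 level requires. The paragraph then closes with a rule that reads as two-sided: p below 0.05 matched to a 95% interval. A one-sided 0.05 test would match a 90% two-sided interval.

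What is at stake is the criterion for claiming benefit. If the one-sided level governs, the chance of falsely claiming benefit is 5%. If the two-sided rule governs, it is 2.5%. A result favouring HCQ with a two-sided P between 0.05 and 0.10 has a one-sided P between 0.025 and 0.05, so it succeeds under one rule and fails under the other. This is not detail that could wait for a statistical analysis plan, because the protocol itself gives two statements that disagree.

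**Working it through.** **Inputs** (all from the sample size paragraph): control 0.20, HCQ 0.10, difference 0.10, mean rate 0.15, power 80% (z = 0.842), 1:1 allocation. z is 1.645 for one-sided 0.05 and 1.960 for two-sided 0.05.

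**Formula** (pooled variance, no continuity correction), per group:

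n = [z_α·√(2·0.15·0.85) + 0.842·√(0.20·0.80 + 0.10·0.90)]² / 0.10²

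The two roots are √0.255 = 0.505 and √0.25 = 0.500.

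**Step 1: the plan's inputs as written (one-sided).** (1.645·0.505 + 0.842·0.500)² / 0.01 = 156.6, so 157 per group (314 in total). This does not reproduce 200.

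**Step 2: two-sided 0.05.** (1.960·0.505 + 0.842·0.500)² / 0.01 = 199.0, so 199 per group (398 in total). This does reproduce 200.

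**Step 3: does another standard formula rescue the one-sided reading?**

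| Variant | One-sided, per group | Two-sided, per group |
|---|---|---|
| Pooled | 157 | 199 |
| Unpooled | 155 | 197 |
| Arcsine | 154 | 195 |
| Continuity-corrected | 177 | 219 |

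No one-sided variant comes near 200. The three uncorrected two-sided variants do.

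**Step 4: another possible origin.** The same formula at one-sided 0.05 with the pilot rates has mean rate 0.1505 and difference 0.089:

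(1.645·√(2·0.1505·0.8495) + 0.842·√(0.195·0.805 + 0.106·0.894))² / 0.089² = 198.5, so 199 per group.

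The number could therefore have come from the pilot rates at a one-sided level. The text, however, gives 20% and 10% as the anticipated rates, so one printed input is wrong on either account.

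**Step 5: power at 200 per group, 20% against 10%.** The normal approximation is Φ[(0.10·√200 − z_α·0.505)/0.500]. One-sided this is Φ(1.167) = 87.8%; two-sided it is Φ(0.849) = 80.2%. Exact power, obtained by summing binomial probabilities over all pairs of counts at which each test rejects:

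| Test | One-sided 0.05 | Two-sided 0.05 |
|---|---|---|
| Uncorrected chi-square | 88.4% | 81.1% |
| Yates-corrected chi-square | 85.4% | 76.8% |
| Fisher's exact | 85.4% | 76.8% |

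**The case against.** The strongest reply is that the error does no harm to power. If the one-sided level is meant, 200 per group exceeds the 157 needed. If the two-sided level is meant, the uncorrected test still has 81.1%. This stands, and it means the point is not that the trial is too small.

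A reader might infer from the named tests that the trial misses its 80%. The document does not support that without a condition. At the one-sided level it states, Yates and Fisher both give 85.4%. The shortfall of about 3 points (76.8%) arises only on the two-sided reading, and if all 220 per group were evaluable the two-sided figures would be 80.7% and 81.1%.

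It is also fair to say that the sidedness of the analysis is never stated. The two-sided reading is an inference from pairing p below 0.05 with a 95% interval, and Fisher's test can be run one-sided. The inference is the natural one, but it remains an inference. Likewise, a reader might take the match with 199 as proof that a two-sided calculation was run; step 4 shows why it is not.

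Two further criticisms are tempting and should not be made. Recruiting 440 to allow for 10% dropout leaves 440 × 0.9 = 396, but the target is given only as approximate, so a gap of 4 is immaterial. Nor is it an error that power at the pilot rates is not reported: the protocol chooses its design rates openly and prints the pilot rates beside them.

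**Conclusion.** The point holds in this form. The stated size does not follow from the stated inputs: 157 per group is needed, against 200 stated. The level used for sizing also conflicts with the significance rule in the same paragraph. In planned power the discrepancy is benign or small, ranging from about 88% (one-sided, uncorrected) to about 77% (two-sided, Yates or Fisher). The material consequence is the undefined criterion for success, with a false-claim rate of 5% or 2.5% and opposite conclusions when a two-sided P favouring HCQ lies between 0.05 and 0.10.

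The conclusion rests on the printed rates of 20% and 10%, equal groups, independent participants, and reading a 95% interval as two-sided. It does not depend on knowing how 200 was obtained.

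**What to change.** In the sample size paragraph, state a two-sided 0.05 level for the calculation, and state that the same two-sided 0.05 rule, with its 95% confidence interval, decides the primary comparison. This agrees with both the interval and the 200 per group already in the text, so only the word describing sidedness has to change.

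Name one primary test and give its power at that level for 20% against 10% with 200 per group: about 81% for the uncorrected chi-square, or about 77% if the Yates-corrected chi-square or Fisher's exact test is kept. Either choice is valid; what matters is that the stated power belongs to the test that will be used.

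The cost is a change of wording. The only downside is a slightly less favourable stated power if the corrected or exact test is kept.
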